### Online Modules

The modules are designed for individuals who experience symptoms of anxiety and depression in the context of COVID-19 pandemic. We combined our expertise in content development [20] from previous clinical trials, which used a similar approach to address depression [21] and anxiety [12], and certain content from previous therapeutic modules, and adapted them to address COVID-19–related stressors and develop relevant strategies. We then discussed the content with an expert panel of therapists, psychiatrists, and end users to ensure the suitability and efficiency of the content. During this program, therapists will help participants understand that in any given situation, their thoughts, feelings, and actions all interact with and influence one another and help them change their thoughts and actions. The goal of this program is to teach individuals how to identify and change their destructive and disturbing thought patterns, which have a negative influence on behavior and emotions. Through these modules, we will discuss the effect of the pandemic on mood, the basics of CBT, deep breathing techniques, body scan and meditation, the self-care kit, SMART (Specific, Measurable, Achievable, Realistic, and Timely) goals, thinking errors, 5-part models, and thought records. The first 2 sessions will be designed to address symptoms caused by the fear of illness and concerns about personal safety in the context of the pandemic. The rest of the sessions will focus on cognitive and behavioral techniques, problem-solving techniques, and mindfulness practices to help build healthy coping skills that address the uncertainties surrounding the COVID-19 pandemic and the symptoms of depression and anxiety. During this program, we will focus on essential thinking and behavioral skills to help individuals become more engaged in day-to-day activities. We will also work on evaluating negative beliefs and thought processes, as well as their relationship with anxiety/depression. Our goal is to adjust negative thinking so that participants can think about and adapt to the things that are happening to them. This will allow participants to adjust the way they behave, think about their problems in a way that is not as negative, and replace negative thoughts with potentially more positive and productive thoughts and behaviors.

In addition to the content, we pay special attention to the presentation of materials to participants. There are multiple animations and interactive examples that will be provided in each session to keep the participants interested and engaged, such as those in the OPTT Inc sample session [19]. The modules are accessible with any device (ie, desktops, tablets, and cellphones) and compatible across multiple browsers.

### Training

All the therapists are research assistants hired by the research team. These therapists have previous training in psychotherapy, and they will receive further training from one of the psychiatrists involved in the study before they interact with participants. Therapists will learn the standard care pathway, aim, and content of each therapeutic session. Moreover, they will be provided with sample homework from patients and asked to provide feedback as practice for each session. As explained earlier, the feedback templates will vary from session to session, and therapists will personalize each template for each patient’s homework. Training will be provided through webinars and exercises with feedback. Therapists will also be supervised by the lead psychiatrist on the team, who has more than 10 years of experience in in-person and online psychotherapy. After the feedback is prepared by the therapist, the feedback will be read, edited, and approved by the supervisor before it is submitted to the participant.

During the consent process, participants are informed that this program is not to be used as a crisis resource, as therapists cannot be reached at all times through the OPTT platform. In the case of an emergency (eg, suicidal ideation), therapists will be instructed to direct patients to the proper resources (eg, emergency department, crisis lines, etc) and inform their supervisor about such incidents.

### Ethics and Data Privacy

All procedures have been approved by and comply with the Queen’s University Health Sciences and Affiliated Teaching Hospitals Research Ethics Board. Only the care providers involved in the care of the participant will have access to their participant’s information. Hard copies of consent forms and participant identity will be securely stored on-site and destroyed 5 years after study completion. Participants will only be identifiable by an ID number on the OPTT platform, and only anonymized data will be provided to the analysis team members.

To ensure data privacy and security, the care platform (ie, the OPTT) was developed so that it complies with the Health Insurance Portability and Accountability Act, Personal Information Protection and Electronic Documents Act, and Service Organization Control-2. All servers and databases are hosted in the Amazon Web Service Canada cloud infrastructure, which is managed by Medstack (Medstack Inc) [22], to ensure that all Canadian provincial and federal privacy and security regulations are met. For privacy purposes, the OPTT will not collect any identifiable personal information or internet protocol addresses from participants. The OPTT will only collect anonymized metadata to improve its service quality and provide advanced analytics data to the clinical team. All data will be encrypted by the OPTT, and no employee will have direct access to participant data. All encrypted backups are to be kept in the Amazon S3 storage that is dedicated to Queen’s University, Kingston, Ontario, Canada.

### Outcome Evaluation

Primary outcome measures will be anxiety level based on Generalized Anxiety Disorder-7 (GAD-7) Item Questionnaire scores, depression level based on Patient Health Questionnaire-9 Item scores, resilience level based on Resilience Scale-14 Item Questionnaire scores, and quality of life based on Quality of Life and Enjoyment Questionnaire scores. All questionnaires will be collected directly through the OPTT at baseline, prior to week 5, and after the last session.

In addition to these quantitative measurements, qualitative analyses will be performed to evaluate the efficacy and feasibility of providers delivering e-CBT and participants receiving e-CBT. Health care providers will be asked about the feasibility of providing e-psychotherapy and how it compares to in-person psychotherapy in terms of time commitment, feelings of connectedness to the participant, and any perceived benefits and drawbacks to e-psychotherapy. Information on personal, social, and cultural factors (eg, gender, sexuality, background, supportive resources, structural/social barriers, etc) will be extracted from focus groups using an interpretive phenomenological analysis approach. Additionally, participants will be asked about their experiences with using the OPTT and their positive or negative experiences with the e-CBT program. Program adherence and completion rates will also be recorded and reported.

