
In this protocol, we aim to develop a scalable online psychotherapy clinic centered around e-CBT to assist patients with stress resulting from the COVID-19 pandemic. The e-CBT program consists of 9 weekly modules that focus on coping skills and building resilience, which are effective in the treatment of mood and anxiety disorders. We will use the Online Psychotherapy Tool (OPTT; OPTT Inc) [18], a secure, cloud-based platform, to interact with patients and deliver therapy. By using the OPTT, all patient information can be kept secure and confidential, while allowing all clinicians on the treatment team to access their patients’ information and communicate with one another through the platform to discuss their patients. We hypothesize that using these psychotherapeutic interventions during the COVID-19 pandemic will improve the quality of life and decrease symptoms of depression and anxiety in the intervention group compared to the control group.

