### Data Analysis

Initially, all data will be examined for missing, nonsensical, and outlying variables. Missing data will be treated as missing and not imputed. This will be analyzed on a per-protocol basis. Given the likelihood of participant drop out or withdrawal, we have purposely oversampled our study and control groups to obtain meaningful and statistically significant results at the end of the study. Based on our previous experience with CBT and e-CBT in similar patient populations, we anticipate that up to 30% of participants will drop out by the end of the treatment or TAU phases. Using GAD-7 questionnaire scores as the primary outcome means that a 30% change is considered clinically significant. Therefore, a sample size of 40 participants in each arm of the study will be sufficient for detecting significant results (ie, *P*=.05 and a power of 0.95). In addition, an intention-to-treat analysis will be performed to evaluate completion rates and the clinical effects of participants leaving the trial before completion.

Data collection will occur at 3 separate time points, as follows: at baseline (ie, preintervention), in the middle of the study (ie, week 5), and immediately at postintervention (ie, week 9). Mann-Whitney U tests will be used to compare baseline demographic data between individuals who drop out and those who finish the e-CBT program, and any fundamental differences between completers and noncompleters will be identified. A linear regression analysis for continuous outcomes and binomial regression analysis for categorical outcomes will be performed to identify variables associated with the 2 outcome measures over the 3 measurement time points and to compare the differences between study arms. These analyses will be controlled for demographic variables, such as age and gender.

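### The primary outcome is defined inconsistently: four measures are called primary, the sample size rests on GAD-7 alone, and the analysis refers to two unidentified outcome measures

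*Protocol article*

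**What the plan says.** The Protocol article describes its main outcome in four places.

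- **Outcome Evaluation:** "Primary outcome measures will be anxiety level based on Generalized Anxiety Disorder-7 (GAD-7) Item Questionnaire scores", followed in the same sentence by "depression level based on Patient Health Questionnaire-9 Item scores" and by "resilience level based on Resilience Scale-14 Item Questionnaire scores, and quality of life based on Quality of Life and Enjoyment Questionnaire scores". That makes four primary measures, with no order among them.
- **Data Analysis, sample size:** "Using GAD-7 questionnaire scores as the primary outcome means that a 30% change is considered clinically significant". The next sentence says that 40 participants per arm "will be sufficient for detecting significant results (ie, *P*=.05 and a power of 0.95"). This is the only place where a significance level or a power is given.
- **Data Analysis, second paragraph:** the regressions are meant "to identify variables associated with the 2 outcome measures over the 3 measurement time points and to compare the differences between study arms". The two measures are not identified.
- **Background and Rationale:** the hypothesis is that the intervention will "improve the quality of life and decrease symptoms of depression and anxiety" relative to control. Resilience is not mentioned.

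Scores are collected at baseline, week 5 and week 9. The Results section reports 58 participants recruited (35 intervention, 23 control), with data collection still open.

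**The concern.** The count of main outcomes is four in one section, and then one and apparently two in another. A later analysis plan can add detail, but it cannot make a four-outcome definition and a one-outcome definition both true. Until one is chosen, two things are open:

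- **What decides efficacy.** A reader of the results could not tell from the article which scale had been meant to carry the claim, so the choice could be made after the data are seen.
- **What N=80 delivers.** The stated significance level and power belong to GAD-7. Nothing is said about power for the other three scales, or about power for GAD-7 if the significance level had to be shared among several primaries.

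**Working it through.** **1. The plan's own figure.** The article gives 40 per arm for GAD-7 at P=.05 and power 0.95, with a 30% change as clinically significant. It gives no standard deviation, no baseline mean and no sidedness, and does not say whether the change is within or between arms. The figure can therefore be neither reproduced nor refuted. In standardized terms, two-sided, the detectable difference is (1.960 + 1.645) × √(2/n). For n = 40 that is 3.605 × 0.2236 = 0.81. For the 28 per arm left after 30% dropout (40 × 0.70) it is 3.605 × 0.2673 = 0.96. Either way the calculation concerns one outcome.

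**2. The statements side by side.**

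| Place | Number of main outcomes | Which |
|---|---|---|
| Outcome Evaluation | 4 | GAD-7, PHQ-9, Resilience Scale-14, quality of life |
| Data Analysis, sizing | 1 | GAD-7 |
| Data Analysis, regression | 2 | not named |
| Background and Rationale, hypothesis | 3 | quality of life, depression, anxiety |

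**3. False-positive rate under different success rules.** The article states none of the following, so they are assumptions: two-sided tests at .05 for each outcome, one test per scale, and an equal pairwise correlation ρ between the test statistics.

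For independent tests the rate is 1 − 0.95^k:
- four outcomes: 1 − 0.95⁴ = 1 − 0.8145 = 18.5%
- two outcomes: 1 − 0.95² = 1 − 0.9025 = 9.75%

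For correlated tests the rate is 1 − ∫ φ(u) [Φ((1.96 − √ρ u)/√(1−ρ)) − Φ((−1.96 − √ρ u)/√(1−ρ))]^k du, integrated numerically. A simulation of 1,000,000 draws agrees to within about 0.1 percentage point.

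| ρ | any of four | any of two |
|---|---|---|
| 0 | 18.5% | 9.75% |
| 0.3 | 17.4% | 9.5% |
| 0.5 | 15.6% | 9.1% |
| 0.7 | 13.0% | 8.3% |
| 0.8 | 11.4% | 7.8% |
| 0.9 | 9.4% | 7.0% |

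If all outcomes must be significant, or if GAD-7 alone is primary, the rate is at most 5%.

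**4. Power if several primaries are kept.** Take a design that has exactly 95% power at two-sided .05, so that the expected test statistic is about 1.960 + 1.645 = 3.605.
- Four primaries, Bonferroni .0125 each (critical value 2.498): power per outcome is Φ(3.605 − 2.498) = Φ(1.107) = 86.6%. Holding 95% multiplies n by ((2.498 + 1.645)/3.605)² = 1.32, so 40 per arm becomes 53.
- Two primaries, .025 each (critical value 2.241): power is Φ(3.605 − 2.241) = Φ(1.363) = 91%. The multiplier is ((2.241 + 1.645)/3.605)² = 1.16, so 40 per arm becomes 47.

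These powers assume that each scale has the same standardized effect as the one used for GAD-7, which the article does not say.

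**The case against.** The strongest reply is that only a condensed article is shown. Success rules and multiplicity adjustment are commonly left to the full protocol or the analysis plan, so their absence here is not a fault. That stands, and the point does not rest on it.

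A reader might infer that each of the four outcomes is to be tested at .05 and that the trial therefore carries a 13-19% false-positive rate. The article does not support this. P=.05 appears once, in the GAD-7 sizing sentence, and no any-of-four rule is written anywhere. The only efficacy hypothesis joins its outcomes with 'and', which fits an all-must-succeed reading at least as well. The correlations are also assumed, and above 0.7 the four-outcome rate falls below 13%. Nor is there a stated plan to claim success at week 5 separately; a regression over three time points need not imply one.

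The two outcome measures may mean the two outcome types, continuous and categorical, named earlier in the same sentence. That is possible, although Outcome Evaluation defines no categorical outcome. If it is right, the two-outcome count drops away but the four-versus-one conflict stays. The omission of resilience from the hypothesis is weak evidence by itself, since a hypothesis need not list every measure.

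Finally, the intervention group consists of those who accept e-CBT and the control group of those who decline it, so chance error is not the main threat to an efficacy claim. That is true, and the article acknowledges the nonrandomized design as a limitation. It does not remove the need to know which outcome decides.

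**Conclusion.** The contradiction is in the text and does not depend on any document not shown: four unranked primary outcomes in one section, GAD-7 as the primary outcome in the next. The stated P=.05 and power of 0.95 apply to one of the four.

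The effect on error is conditional on a rule that the article leaves open: 18.5% down to 13% (ρ from 0 to 0.7) if any of four at .05 suffices, about 8-10% over the same correlations if any of two suffices, and no more than 5% if all must succeed or GAD-7 alone is primary. If four primaries were kept under Bonferroni, a nominal 95% power would be about 87% per outcome. All of these are chance error rates and say nothing about bias from self-selected groups. The point should be settled before analysis, because the correction loses much of its value once results are known.

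**What to change.** Before any outcome analysis, name GAD-7 at week 9, e-CBT versus TAU, as the single primary outcome. This matches the sizing sentence, and week 9 matches its dropout allowance, which runs to the end of the treatment or TAU phase. List PHQ-9, quality of life and resilience as secondary, treat week 5 as supportive, and replace the reference to two outcome measures with the outcomes meant.

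The cost is a change of text with no change in N. Three scales lose primary status. Because 58 of the planned 80 participants were already recruited, this is a mid-trial change to a registered study: date it, give the reason, and record that it was made before outcome data were analysed.

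The alternative is to keep more than one primary, for example GAD-7 and PHQ-9 because participants with MDD are enrolled as well as those with GAD. Then state whether one or all must succeed. If one is enough, control the familywise error, for instance by Holm. In either case restate the power. With two primaries, a nominal 95% becomes about 91% at the first Holm step (.025), or 47 per arm to hold 95%. With four under Bonferroni it becomes about 87%, or 53 per arm.

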### Data Analysis

Initially, all data will be examined for missing, nonsensical, and outlying variables. Missing data will be treated as missing and not imputed. This will be analyzed on a per-protocol basis. Given the likelihood of participant drop out or withdrawal, we have purposely oversampled our study and control groups to obtain meaningful and statistically significant results at the end of the study. Based on our previous experience with CBT and e-CBT in similar patient populations, we anticipate that up to 30% of participants will drop out by the end of the treatment or TAU phases. Using GAD-7 questionnaire scores as the primary outcome means that a 30% change is considered clinically significant. Therefore, a sample size of 40 participants in each arm of the study will be sufficient for detecting significant results (ie, *P*=.05 and a power of 0.95). In addition, an intention-to-treat analysis will be performed to evaluate completion rates and the clinical effects of participants leaving the trial before completion.

Data collection will occur at 3 separate time points, as follows: at baseline (ie, preintervention), in the middle of the study (ie, week 5), and immediately at postintervention (ie, week 9). Mann-Whitney U tests will be used to compare baseline demographic data between individuals who drop out and those who finish the e-CBT program, and any fundamental differences between completers and noncompleters will be identified. A linear regression analysis for continuous outcomes and binomial regression analysis for categorical outcomes will be performed to identify variables associated with the 2 outcome measures over the 3 measurement time points and to compare the differences between study arms. These analyses will be controlled for demographic variables, such as age and gender.

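### The efficacy analysis is per-protocol without imputation at up to 30% expected dropout, so it may be biased, plausibly towards e-CBT, and the added intention-to-treat analysis names no method for missing week-9 scores

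*Protocol article*

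**What the plan says.** All of the relevant rules stand in the Data Analysis section of the protocol article.

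- **Missing data and analysis set:** "Missing data will be treated as missing and not imputed. This will be analyzed on a per-protocol basis". The article does not define the per-protocol population.
- **Expected loss:** "we anticipate that up to 30% of participants will drop out by the end of the treatment or TAU phases". This covers both arms.
- **Remedy for loss:** "we have purposely oversampled our study and control groups to obtain meaningful and statistically significant results at the end of the study".
- **Second analysis:** "an intention-to-treat analysis will be performed to evaluate completion rates and the clinical effects of participants leaving the trial before completion". No method for missing outcomes is attached to it.
- **Model:** linear regression for continuous outcomes and binomial regression for categorical ones, using scores from baseline, week 5 and week 9, adjusted for demographic variables such as age and gender. No mixed or other likelihood-based longitudinal model is named.
- **Completer check:** Mann-Whitney tests of baseline demographics, dropouts against finishers, for the e-CBT program only.

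Two other sections bear on the point. Participants describes a nonrandomized allocation in which people who decline e-psychotherapy form the TAU control group. Outcome Evaluation places the final questionnaires after the last session and has them collected through the online platform.

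**The concern.** A per-protocol analysis without imputation estimates the effect among those who stay. If those who leave fare differently from those who stay, and differently by arm, the comparison is biased.

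The two arms do not ask the same of participants. e-CBT requires weekly modules of about 40 minutes and homework, while TAU is the continuation of existing care. A filter on completing the program would therefore tend to select engaged people in one arm, and the timing of the last questionnaire ties the e-CBT outcome to finishing. This selection would come on top of the self-selection already present in a nonrandomized design.

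The article plans rapid dissemination and uptake by other practices. For that purpose the useful quantity is the effect among everyone who starts e-CBT. If the intention-to-treat comparison at week 9 also rests on observed cases only, it gives little check on the per-protocol result.

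**Working it through.** **1. The plan's own figure.** The article states that "a sample size of 40 participants in each arm of the study will be sufficient for detecting significant results", with significance level 0.05 and power 0.95. It cannot be reproduced, because no baseline mean, standard deviation, control-arm change or responder rate is given. Two things can be derived:

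- With 30% loss, 40 × 0.70 = 28 completers per arm. Equally, 28 / 0.70 = 40, so 40 is consistent with 28 inflated for dropout, but the article does not say whether 40 is before or after inflation.
- The implied standardized difference (two-sided, normal approximation) is (1.960 + 1.645) × √(2/n). This gives 0.81 for n = 40 and 0.96 for n = 28.

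So oversampling concerns how many remain. The next step shows that it does not bear on bias.

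**2. Bias of a completer comparison.** Let D be the completer difference between arms in mean improvement. Let p_E and p_T be the dropout proportions in e-CBT and TAU, and let x and y be the amounts by which dropouts improve less than completers in e-CBT and TAU.

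- All-participant difference = D − p_E·x + p_T·y
- Bias of the completer analysis = p_E·x − p_T·y

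No sample size appears in the bias, so a larger trial leaves it unchanged.

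**3. Size when only e-CBT dropouts differ.** Take y = 0 and let e-CBT dropouts keep a share f of the benefit D, so x = (1 − f)·D. The completer effect divided by the all-participant effect is 1 / [(1 − p_E) + p_E·f]. Both f and y = 0 are assumptions. The document gives neither.

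| e-CBT dropout | f = 0 | f = 0.5 |
|---|---|---|
| 10% | 1/0.90: +11% | 1/0.95: +5% |
| 20% | 1/0.80: +25% | 1/0.90: +11% |
| 30% | 1/0.70: +43% | 1/0.85: +18% |

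**4. Size when TAU dropouts differ too.** Assume 30% dropout in both arms, with completers improving by 5 points (e-CBT) and 1 point (TAU), so the completer difference is 4. All of these values except the 30% are illustrative.

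| x (e-CBT shortfall) | y (TAU shortfall) | All-participant difference | Completer analysis |
|---|---|---|---|
| 4 | 0 | 4 − 1.2 = 2.8 | overstates |
| 2 | 0 | 4 − 0.6 = 3.4 | overstates |
| 4 | 4 | 4 − 1.2 + 1.2 = 4.0 | unbiased |
| 2 | 4 | 4 − 0.6 + 1.2 = 4.6 | understates |
| 0 | 4 | 4 + 1.2 = 5.2 | understates |

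**5. What the intention-to-treat analysis can use.** A person who leaves after the week-5 assessment has two scores, and a regression across the three time points could use them. A person who leaves before it has a baseline score only. Neither has a week-9 score. Under the no-imputation rule, an ordinary regression of week-9 outcome on group therefore runs on observed cases.

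**The case against.** The strongest reply has four parts.

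- **Dropouts are not necessarily excluded from the intention-to-treat analysis.** A reader might infer that it cannot include them. The text does not support that. Everyone counts towards completion rates, those who leave after week 5 have two usable scores, and declining to impute is not the same as deleting incomplete cases. What stands is narrower: no method is named for participants without a week-9 score, and the named regression would, for an end-of-treatment comparison, fall back to observed cases.
- **Overstatement is not shown.** A reader might also infer that the effect will be overstated. The article expects loss in the TAU phase too, gives no dropout pattern by arm or outcome, and does not define the per-protocol set. The bias could be zero or reversed. This objection stands in full.
- **There are partial safeguards.** Completers and noncompleters are compared, adherence and completion are to be reported, the nonrandomized design is acknowledged as a limitation, and a randomized study is planned. These help interpretation but do not correct the estimate. The completer comparison covers baseline demographics only, not symptom severity or week-5 response, and leaves out TAU dropouts.
- **Detail may sit in a fuller plan.** That would answer a complaint of silence. It does not answer a rule that the article states outright.

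**Conclusion.** The point holds as a risk of bias fixed by the stated rule. With up to 30% dropout expected, a per-protocol analysis without imputation can misstate the effect of offering e-CBT, and oversampling cannot repair that. Bias towards e-CBT is the more plausible direction given the unequal demands of the arms, but the documents establish neither direction nor size.

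The figures of 43% and 18% at 30% e-CBT dropout rest on two assumptions from outside the document: that TAU dropouts resemble TAU completers, and that e-CBT dropouts keep none or half of the benefit. Equal losses in both arms give zero bias, and relatively worse TAU dropouts give understatement. The intention-to-treat analysis is under-specified for missing week-9 outcomes. It is not shown to be empty.

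**What to change.** Amend the Data Analysis section before analysis begins:

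1. **Primary analysis:** all enrolled participants in the group they joined, by a likelihood-based repeated-measures model on all observed baseline, week-5 and week-9 scores. It is valid if data are missing at random and needs no imputation, so the present rule on that can stay.
2. **Sensitivity analysis:** one missing-not-at-random scenario, for example no improvement after dropout, applied to both arms. Lending e-CBT dropouts the TAU course would be a doubtful choice here, because the TAU arm consists of people who declined e-CBT.
3. **Supportive analysis:** per-protocol, with its population defined for each arm.

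The cost is revised wording and slightly more analysis, with no new visits and no change in sample size. The estimated effect may come out smaller than among completers. The change does not remove the self-selection into arms, which remains a separate limitation.

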The control group will continue receiving TAU for the first 9 weeks of their participation. If control group participants continue to present significant symptoms (ie, <50% reduction in symptoms compared to those in baseline), they will again be offered the option to undergo the e-psychotherapy program or other forms of treatments as deemed necessary.

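### The stated power of 0.95 with 40 per arm does not follow from a 30% change on GAD-7; at 30% dropout it needs a standardized between-arm difference of about 0.98

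*Protocol article*

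**What the plan says.** The sample-size reasoning is in the Data Analysis section of the protocol article. It anticipates losses: "we anticipate that up to 30% of participants will drop out by the end of the treatment or TAU phases". It says both groups were oversampled for this reason. It then gives the effect on which the size rests: "Using GAD-7 questionnaire scores as the primary outcome means that a 30% change is considered clinically significant". The next sentence draws the conclusion, "Therefore, a sample size of 40 participants in each arm of the study will be sufficient for detecting significant results", at P=.05 and "a power of 0.95".

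The same section leaves missing values unimputed, analyses per protocol with an additional intention-to-treat analysis, and plans regression models that compare the two arms and control for demographic variables such as age and gender. The Procedures section describes the comparator: "The control group will continue receiving TAU for the first 9 weeks of their participation". Under Participants, TAU may include medication and psychiatric consultation.

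For the power calculation the article states no SD, baseline mean, expected change under TAU, response rate, sidedness or test.

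**The concern.** The planned comparison is between arms. Its power depends on the difference between the two arms' mean scores relative to the SD. A percentage change described as clinically significant is neither of those. It reads most naturally as a threshold for one person's improvement, though the article does not say so. Even if it is read as a difference between arms, it still needs a baseline mean to become points and an SD to become an effect size. If it is the improvement expected with e-CBT, the improvement expected under TAU must also be subtracted. The word that opens the conclusion presents 40 per arm and 0.95 as consequences of the 30%, and they are not.

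The stake is interpretation. A reader who is told the power was 0.95 would take a null result as strong evidence against a worthwhile effect. The Results and Discussion sections plan rapid dissemination to other clinicians and a randomized follow-on study, and the figure could be carried into both.

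**Working it through.** **Inputs from the Data Analysis section.** 40 enrolled per arm; alpha 0.05; power 0.95; dropout up to 30%; per-protocol analysis without imputation; comparison between arms.

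**Assumptions, because the article gives no values.** Two-sided unadjusted t-test; GAD-7 baseline mean M of 12-15; common SD of 4-5; TAU improvement c of 0% or 10% of baseline.

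**1. Reproducing the plan's figure.** It cannot be reproduced, since no SD, mean, TAU change or response rates are stated. Literal readings of 30% do not give 0.95 either:
- As a standardized difference of 0.3: power 0.26 at 40 per arm and 0.20 at 28.
- As a 30-point difference in response rates (control rate assumed 10-35%): 0.78-0.89 at 40 per arm and 0.62-0.75 at 28.
- As a pre-post test within one arm: 95% power needs a standardized change of 0.58 at n = 40 or 0.71 at n = 28. This is not the between-arm comparison.

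**2. Evaluable number.** 40 x (1 - 0.30) = 28 per arm at the upper dropout limit.

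**3. Difference needed.** By the normal approximation, d = (1.960 + 1.645) x sqrt(2/n).
- n = 28: 3.605 x 0.2673 = 0.963; exact noncentral t, 0.981.
- n = 40: 3.605 x 0.2236 = 0.806; exact, 0.816.
- n = 28, one-sided: exact, 0.890.
- n = 28, 80% power, two-sided: exact, 0.762.

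**4. Turning 30% into an effect size.** d = (0.30 - c) x M / SD. The case c = 0 is also the case in which 30% is itself the between-arm difference. Reaching d = 0.981 with c = 0 requires SD/M of at most 0.30/0.981 = 0.306. At SD 5 that means a baseline mean of 0.981 x 5 / 0.30 = 16.4.

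Power at 28 per arm (two-sided 5%):

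| Baseline mean | SD | d, TAU unchanged | Power | d, TAU improves 10% | Power |
|---|---|---|---|---|---|
| 12 | 4 | 0.90 | 0.91 | 0.60 | 0.60 |
| 12 | 5 | 0.72 | 0.75 | 0.48 | 0.42 |
| 15 | 4 | 1.125 | 0.985 | 0.75 | 0.79 |
| 15 | 4.5 | 1.00 | 0.96 | 0.67 | 0.69 |
| 15 | 5 | 0.90 | 0.91 | 0.60 | 0.60 |

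**5. Precision at 28 per arm.** The 95% CI half-width for the difference is t(54) x sqrt(2/28) = 2.005 x 0.2673 = 0.536, or about 0.54 SD.

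**The case against.** A reader might infer that the design does not have 95% power. The documents do not support that. They give no SD, mean or TAU change, and some plausible combinations reach 0.95: baseline 15 with SD 4.5 and no change under TAU gives 0.96, and SD 4 gives 0.985. What stands is that 0.95 is conditional on favourable values the article does not state.

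Four further objections have weight.
- **Analysis model.** The article plans regression, not an unadjusted t-test. If baseline GAD-7 were a covariate with an assumed correlation of 0.5 with the week 9 score, the required difference would fall to 0.981 x sqrt(1 - 0.25) = 0.85; at 0.7 it would be 0.981 x sqrt(1 - 0.49) = 0.70. The article names only demographic covariates. Even at correlation 0.5, a 10% TAU improvement with baseline 12-15 and SD 5 leaves power at 0.53-0.72.
- **Dropout.** 30% is an upper limit, the groups were oversampled for it, and an intention-to-treat analysis is added. So 28 is the low end. With no loss at all the required difference is still 0.82.
- **Article format.** A condensed article may leave the SD and expected means to a full protocol, so their absence alone would be no finding. Here the article itself prints a derivation and a specific power.
- **Multiplicity.** A reader might add that the four primary outcomes under Outcome Evaluation are each tested at an unadjusted 5%. The article is silent on adjustment and sizes the trial on GAD-7 alone, so that cannot be concluded from it.

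**Conclusion.** The point holds as an unsupported derivation. No sum in the article is wrong, and 40 enrolled does correspond to 28 completers at 30% loss. But power 0.95 cannot be obtained from the stated 30%. The results at 28 per arm that need no GAD-7 assumptions are a detectable standardized difference of about 0.98 for 95% power and 0.76 for 80%, under an unadjusted two-sided 5% t-test; one-sided testing lowers the first to 0.89. The power range of about 0.42-0.79 rests on assumed values (baseline 12-15, SD 4-5, TAU improving 10%) and shows how sensitive the claim is to inputs that are not stated. It is not an estimate of the trial's actual power. This should be fixed, but it does not call the enrolment target or the analysis into question.

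**What to change.** Replace the unconditional power statement in Data Analysis with text such as:

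> 40 enrolled per arm (about 28 evaluable at 30% dropout) gives 80% power for a standardized between-arm difference of 0.76 and 95% power for 0.98 on GAD-7 at week 9, two-sided 5%; the expected 95% CI half-width is about 0.54 SD.

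If any power figure is kept, state beside it the assumed between-arm difference, SD, change under TAU, sidedness and test, and say whether the 30% is a per-person threshold or a difference between arms. If baseline GAD-7 is to be a covariate, say so and give the assumed correlation.

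The cost is one or two sentences and a less favourable figure. No added enrolment and no change of endpoint or analysis is needed.
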